**Fig. 1 Fig1:**
[figure not shown]
Summary of the IMA-cRCT Research Project and timeline

The intervention assignment is cluster-based considering PC teams and two parallel arms: usual care in the control group and the IMA intervention in the intervention group. Twenty-four PC teams will participate in the trial.

The Standard Protocol Items: Recommendations for Interventional Trials (SPIRIT) checklist for study protocols [55, 56] is provided in Additional file 1. Details about the pragmatic design of the IMA-cRCT are provided in the Pragmatic Explanatory Consortium Indicator Summary (PRECIS-2) [57] wheel scheme in Additional file 2.

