### Study population

#### PC teams, GPs, and nurses

##### Recruitment and selection

The recruitment process follows both top-down and bottom-up approaches to identify and recruit PC teams and healthcare professionals.

A PC team is a group of GPs, nurses and other healthcare professionals who offer comprehensive care to a specific population. PC teams can work in one or more PC centres and large PC centres can accommodate more than one PC team. PC teams from all over Catalonia managed by the Catalan Health Institute will be assessed for eligibility (*n* = 287). A list of PC teams and their characteristics will be provided by the System for the Development of Research in Primary Care (SIDIAP). Pairs of PC teams will be randomly selected based on their location (rural/urban) and stratified according to certain non-initiation [9] predictors: PC teams located in urban areas will be stratified according to the number of practitioners in the PC team, the size of the catchment area population for each PC team, the socioeconomic status of the population and the proportion of immigrants; and PC teams located in rural areas will be stratified according to the socioeconomic status of the population. An ordered list of replacement PC teams with the same characteristics will be randomly generated for each pair of PC teams.

To avoid contamination between PC teams and community pharmacies, a maximum of one PC team will be selected for each municipality (in municipalities ≤ 100,000 inhabitants) or single PC teams per neighbourhood (in municipalities > 100,000 inhabitants). In the case of PC teams from adjacent municipalities, there must be a minimum distance of 3 km between each team’s working place. If a PC team does not fulfil the inclusion criteria, the following PC team from the list of replacements will be considered for participation. The inclusion of PC teams from all provinces will be ensured.

Randomly selected PC teams will be informed about the study and invited to participate. First, the PC Territorial Managers and team managers from the selected PC teams will be invited to explain and present them the project and will be asked to encourage GPs and nurses from their teams to take part in the study. If the team manager accepts to participate, the study will then be presented to the GPs and nurses in each team.

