### Randomisation

Paired PC teams included in the study will be randomised (1:1) into two parallel groups using a computerised random number generator. Concealment of allocation was guaranteed at the PC team level: PC teams will not be randomised until both teams in each pair agree to participate in the study. However, at the patient level, it is not possible to guarantee concealment of allocation due to the intrinsic characteristics of the study design by clusters.

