### Statistical analysis

All analyses will be conducted following the intention to treat principle, including all patients treated by the GPs who fulfil inclusion criteria.

Poor registration of clinical outcomes and CVR data in electronic medical records may generate missing values. To deal with missing data, we will first explore the pattern of the missing data by using logistic regression models to test whether the observed variables predict the presence of missing data. If the existence of missing data is indeed explained by observed variables, a Missing at Random pattern will be assumed and multiple imputations with chained equations will be used to impute missing data. If possible, the imputation models will use any covariate that is predictive of missingness as well as all the variables that will be later used in the effectiveness and cost-effectiveness models [80]. The number of imputations will be determined by the fraction of missing information [81, 82]. The subsequent analyses will be conducted in each of the imputed datasets and the estimators will be pooled using Rubin’s rules [81].

A descriptive analysis, based on sociodemographic variables and health problems, will be performed to compare groups at baseline. Characteristics of participating healthcare professionals will also be compared between groups. Continuous variables will be presented with means and standard deviation; categorical variables will be presented with frequency and percentages. Differences between groups in these variables will be estimated using multilevel linear regression for continuous variables and multilevel logistic regression for categorical variables, considering the group as the independent variable in both cases.

The impact of the intervention will be assessed overall and for each pharmacotherapeutic subgroup, i.e., the 3rd level of the Anatomical Therapeutic Chemical (ATC) Classification System [83].

All models will be controlled for patient sociodemographic and clinical characteristics that have been described in the literature as predictors of non-initiation [9, 18] and which show statistically significant differences between intervention and control group at baseline; and will be performed using multilevel techniques. The basic unit of analysis will be either prescription or patient, based on the analysis. All analyses will be clustered at the level of PC team and GP.

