#### Effectiveness

To assess the impact of the IMA intervention on initiation, a multilevel logistic regression will be estimated in which the dependent variable will be initiation and the independent variable will be the group.

A multilevel logistic regression model will be performed to compare the proportion of adherent patients between the intervention and control groups. In the model, the dependent variable will be adherence and the independent variable will be the group.

Multilevel repeated measure models will be used in which clinical parameters and CVR (the dependent variables) are considered several times, at diverse time points during the follow-up period.

The interaction ‘group x time’ will be used to evaluate the impact of the intervention (independent variables).

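### Teams are matched and randomised in pairs, but the stated models include neither the pair nor the team-level matching factors; if the matching is informative, the analysis is conservative and loses power

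*Protocol article*

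**What the plan says.** **Design.** Recruitment and selection (PC teams, GPs, and nurses) states: "Pairs of PC teams will be randomly selected based on their location (rural/urban) and stratified according to certain non-initiation [9] predictors". Urban teams are stratified on number of practitioners, catchment population, socioeconomic status and proportion of immigrants; rural teams on socioeconomic status. Under Randomisation: "Paired PC teams included in the study will be randomised (1:1) into two parallel groups using a computerised random number generator". No pair is randomised until both of its teams have agreed, so the pair is the randomisation block. On numbers, the Design section says: "Twenty-four PC teams will participate in the trial", which makes 12 pairs.

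**Analysis.** Statistical analysis fixes the clustering levels for everything: "All analyses will be clustered at the level of PC team and GP". It also fixes the covariate rule: "All models will be controlled for patient sociodemographic and clinical characteristics that have been described in the literature as predictors of non-initiation", restricted further to characteristics on which the arms differ significantly at baseline. For the primary outcome, the Effectiveness section says "a multilevel logistic regression will be estimated in which the dependent variable will be initiation and the independent variable will be the group". The section Cost-effectiveness analysis adds baseline costs or baseline cardiovascular risk, and nothing about pairs. Rurality, area socioeconomic status and number of GPs are to be collected (Sociodemographic variables and diagnostics), but no model is given them.

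**The concern.** In a matched design, whatever the two teams of a pair share drops out of the difference between arms. A model with random effects for team and GP only does not know this: the shared part remains in its estimate of between-team variance, and hence in the standard error of the group effect.

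The covariate rule does not repair it. Rurality, number of practitioners and catchment size are not patient characteristics, so the rule as written cannot admit them. Patient socioeconomic status and nationality could partly stand in for two of the factors, but only if they are significantly imbalanced, which matching on those factors makes less likely. The rule therefore tends to leave out exactly what the design controlled.

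What is at stake is precision and power on the primary outcome. The protocol itself describes the matching factors as predictors of non-initiation, so some positive within-pair correlation is to be expected.

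**Working it through.** **1. The plan's own figure.** Inputs from Sample size: 10% v 7% non-initiation, 80% power, 5% significance (taken as two-sided), ICC 0.01 for PC teams, 30 prescriptions per GP, 10% losses.

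- Per arm: (1.960 + 0.842)² × (0.10×0.90 + 0.07×0.93) / 0.03² = 1,352.6
- Design effect: 1 + (30 − 1) × 0.01 = 1.29
- Total: 2 × 1,352.6 × 1.29 / 0.9 = 3,877.5, which rounds up to the stated 3,878.

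The figure reproduces, and it contains no term for pairing.

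**2. Variance of a team proportion.** Assume 24 equal teams that deliver the full sample.

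- Analysed prescriptions per team: 3,878 × 0.9 / 24 = 145.4
- Mean binomial variance: (0.0900 + 0.0651) / 2 = 0.07755
- Between teams: 0.01 × 0.07755 = 0.000776
- Within teams: 0.99 × 0.07755 / 145.4 = 0.000528
- Between-team share: 0.000776 / (0.000776 + 0.000528) = 59.5%

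**3. Standard error of the risk difference.** Without the matching: √(2 × 0.001303 / 12) = 0.0147. With 22 df this gives about 49% power. (At team size the design effect is 1 + 144.4 × 0.01 = 2.44, not 1.29. That is a separate matter, but it is why the starting power is below 80%.)

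If matching explains a share r of the between-team variance, the correct value is √(2 × [(1 − r) × 0.000776 + 0.000528] / 12). The documents give no r, so it is varied. Power comes from the non-central t distribution for a difference of 0.03. Type I error comes from simulated unpaired 22-df t-tests on team proportions; the ranges reflect binomial and normal versions of the simulation.

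| r (assumed) | Correct SE | Team-only SE too large by | Power, matching factors as covariates (18 df) | Power, pair effects (11 df) | Type I error, unpaired t-test |
|---|---|---|---|---|---|
| 0% | 0.0147 | 0% | 49% | 46% | about 5% |
| 20% | 0.0138 | 7% | 54% | 51% | 3.7–3.9% |
| 30% | 0.0134 | 10% | 57% | 54% | 3.2–3.4% |
| 50% | 0.0124 | 19% | 63% | 60% | 2.2–2.4% |

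The 18 df are 24 − 2 − 4 for four single-parameter team covariates. Five covariates leave 17 df and change power by less than half a percentage point (53–63% over r = 20–50%). The covariate column assumes that the factors, entered as covariates, capture the same share r.

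**4. When the remedy pays.** Interval width breaks even where the lower variance offsets the larger t quantile.

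- Pair effects: 1 − (2.074 / 2.201)² = 0.112 of the variance of a team proportion; 0.112 / 0.595 = 19% of between-team variance.
- Four covariates: 1 − (2.074 / 2.101)² = 0.026; 0.026 / 0.595 = about 4%.

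**The case against.** The strongest reply is that the loss depends on a quantity nobody has stated. A reader might infer that the standard errors are certainly too large. The documents do not support that: no within-pair correlation is given, nothing shows how tight the matching is, and at r = 0 there is no overstatement. There, pair effects would make matters worse (46% v 49% power). This stands, and the point is conditional for that reason.

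Equal team sizes also flatter the gain in rural pairs. A rural team with the minimum of two GPs has about 2 × 27 = 54 analysed prescriptions, and its between-team share is 0.01 / (0.01 + 0.99/54) = 35%, not 60%. This stands too.

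A reader might go on to charge the plan with using a Wald z-test that ignores the small number of teams, or with bootstrapping the wrong unit. The article states neither a reference distribution nor a resampling unit, and both are commonly left to the analysis plan. The reference distribution does affect the size. If z were used on unpaired teams, type I error would be about 4.9%, 4.2% and 3.0% at r = 20%, 30% and 50%, with power of about 54–55%. Pair effects on 11 df would then gain nothing at 20–30%.

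It can also be said that naming clustering levels does not forbid a stratum term. True, but the article also fixes the covariate rule for all models, and that rule keeps the team-level factors out.

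Nor is the benefit of matching wholly lost: it still balances the arms, whatever the model.

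**Conclusion.** The mismatch between design and analysis is real: the trial randomises within matched pairs, and the models as stated do not reflect the matching. The direction is conservative. Inflated type I error or a biased estimate does not follow from leaving the matching out; the harm is lost precision.

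Under the assumptions used (24 equal teams, ICC 0.01, t-tests on team proportions as an approximation to the multilevel logistic model), the standard error is about 7–19% too large if matching explains 20–50% of between-team variance. Power of about 49% would then be 54–63% with covariates or 51–60% with pair effects. The effect shrinks to nothing as that share goes to zero. This does not invalidate the trial, but it should be corrected because the remedy is nearly free.

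**What to change.** In Statistical analysis, prespecify the matching factors (urban/rural location, area socioeconomic status, number of practitioners, catchment size, proportion of immigrants) as fixed covariates in all effectiveness and cost models. They should enter regardless of any baseline significance test. A random intercept for the randomisation pair is the alternative. In either case, state that tests and intervals use team-level degrees of freedom.

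The covariate form is preferable: it needs only about 4% of between-team variance explained to narrow the interval, against about 19% for full pair effects. Keep each factor to a single parameter where possible, since categories use up further degrees of freedom.

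The cost is a change of wording and a few degrees of freedom. The factors are used to select and pair the teams, so they are known before randomisation and no new data are needed.

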#### Effectiveness

To assess the impact of the IMA intervention on initiation, a multilevel logistic regression will be estimated in which the dependent variable will be initiation and the independent variable will be the group.

A multilevel logistic regression model will be performed to compare the proportion of adherent patients between the intervention and control groups. In the model, the dependent variable will be adherence and the independent variable will be the group.

Multilevel repeated measure models will be used in which clinical parameters and CVR (the dependent variables) are considered several times, at diverse time points during the follow-up period.

The interaction ‘group x time’ will be used to evaluate the impact of the intervention (independent variables).

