### Data collection

The SIDIAP database will be used to collect data for the evaluation of the effectiveness and cost-effectiveness of the IMA intervention. It implies the absence of any *ad-hoc* registry for the sake of the RCT.

SIDIAP gathers information from the electronic medical records of all patients seen by the public PC provider since 2010. This database provides information on patients’ sociodemographic and clinical data, including visits to primary care, health problems, sick leave periods, prescribed medicines, immunisations, laboratory results, clinical outcomes, and information on dispensed medication in any Catalan pharmacy [73]. All these records are dated.

The SIDIAP database is an encrypted, anonymised, secure database. It is managed by the Catalan Health Institute and CatSalut and provides real-world health data generated by the public health system in Catalonia to the scientific community under the legal and regulatory framework, following ethical principles, and maintaining transparency concerning the public program [74].

The SIDIAP database will be used to identify all patients that fulfil inclusion criteria to define the cohort of patients. They will be identified based on GP prescriptions. All variables will be collected for this cohort. All patient-related outcomes will be obtained from the encrypted and anonymised RWD databases. Patients’ personal information will not be provided to the research team. For each patient, data will be collected for the 12 months before the index prescription (for adjustment purposes) and from the subsequent 12 months (follow-up). Figure 3 depicts the observation periods in which the intervention is applied to patients. Information on healthcare professionals will be gathered through questionnaires at the training sessions [53].

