##### Secondary outcome measures

*Secondary adherence*: Implementation during the follow-up period will be calculated 
based on the proportion of days covered (PDC). PDC is the number of days in which 
17
the prescribed medication is available divided by the number of days of the period 
when the prescription is active within the study period (365 days). This value ranges 
from 0 to 1 and is multiplied by 100 to obtain a percentage of adherence [75]. PDC has 
been proved to represent patient behaviour and treatment continuity [76, 77] accurately.
Persistence will be defined as the time from initiation until discontinuation of the 
prescribed treatment, accepting a gap no longer than two months. Patients will be 
classified as adherent or otherwise by combining these two variables; that is, patients 
with PDC>80% during the follow-up year, with medication gaps up to 2 months, will be 
considered adherent.*Reduction of CVR*: The Framingham Risk Score will be calculated using clinical outcomes, like diabetes diagnosis, total cholesterol, high-density lipoprotein cholesterol, systolic and diastolic blood pressure, and sociodemographic variables including age and sex, and tobacco use [78] one year after the index prescription.

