##### Other outcome measures

These data will be collected from the SIDIAP database for the 12 months after the index prescription.*Clinical parameters:* Clinical parameters assessed will depend on the diagnosis. Patients with type II diabetes: glycated haemoglobin, glomerular filtration rate, impaired fasting glucose; with dyslipidaemia: high-density lipoprotein, low-density lipoprotein and total cholesterol; and with hypertension: systolic and diastolic blood pressure.*Cardiovascular events:* Events related to CVD and diabetes, categorised according to the International Classification of Diseases, 10th version (ICD10). Table 2 shows the list of events considered.

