##### Cost-effectiveness analysis

The difference in costs between groups will be estimated using multilevel generalised linear regression models with total costs as dependent variables. Due to the unpredictability in the distribution of costs, various distribution families and link functions will be tested and Akaike and Bayesian information criteria (AIC and BIC) will be used to choose the model with the best fit (usually the gamma distribution with a logistic link). The models will be controlled additionally for baseline costs (those incurred in the 12 months preceding the index prescription).

The difference in effects between groups will be estimated with multilevel regression models. For CVR reduction, multilevel linear regression models adjusted also for baseline CVR will be used. For secondary analyses, the difference in the probability of initiation and secondary adherence between groups will be estimated using a multilevel logistic regression with medication initiation or secondary adherence as the dependent variables.

The ICER will be calculated by dividing the difference in costs between groups by the difference in effects between groups.

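### Read as written, group x time on post-index values misses an early, sustained effect on CVR and clinical parameters, and it does not match the one-year CVR outcome or the CVR model behind the ICER

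*Protocol article*

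**What the plan says.** All places are in the protocol article.

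- **Effectiveness.** CVR and clinical parameters are the dependent variables of multilevel repeated-measures models, in which they "are considered several times, at diverse time points during the follow-up period". The effect parameter is then named: "The interaction ‘group x time’ will be used to evaluate the impact of the intervention".
- **Data collection.** For each patient, "data will be collected for the 12 months before the index prescription (for adjustment purposes) and from the subsequent 12 months (follow-up".
- **Other outcome measures.** For clinical parameters and events: "These data will be collected from the SIDIAP database for the 12 months after the index prescription".
- **Secondary outcome measures.** The outcome is called a reduction of CVR, but the risk score is calculated at one time, "one year after the index prescription".
- **Statistical analysis.** All models are controlled for published predictors of non-initiation "which show statistically significant differences between intervention and control group at baseline". The baseline value of the outcome is not named.
- **Cost-effectiveness analysis.** "For CVR reduction, multilevel linear regression models adjusted also for baseline CVR will be used".

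**The concern.** A group x time interaction measures how the difference between arms changes from the first modelled value onwards. If that first value is already post-index, any difference reached by then and later maintained goes into the group main effect and leaves nothing for the interaction.

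The design makes an early effect plausible. Initiation is judged on dispensing within one month of the prescription, and Strengths and limitations describes the intervention as a single contact and raises the risk that patients collect the medicine only once. If an early difference faded, the arms would converge and the interaction would point against the intervention despite a real early benefit.

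At stake is the effectiveness conclusion on a named secondary outcome and on the clinical parameters. CVR is also the leading effect measure in the short-term economic analysis, where initiation and adherence are assigned to secondary analyses. The report could therefore show no CVR effect in one section and a non-zero CVR effect in the ICER.

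**Working it through.** **1. The plan's own figure.** The document gives no power for CVR or clinical parameters. Its only sample size figure is for initiation: 10% v 7%, 80% power, 5% two-sided (sidedness assumed), ICC 0.01, 30 prescriptions per GP, 10% losses.

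- Per arm: (1.96 + 0.8416)² × (0.10×0.90 + 0.07×0.93) / 0.03² = 1,352.6.
- Design effect: 1 + 29×0.01 = 1.29.
- Total: 2 × 1,352.6 × 1.29 / 0.9 = 3,877.5, i.e. the stated 3,878.

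That figure is not in dispute. After losses it leaves 3,878 × 0.9 / 2 = 1,745 per arm, used below. These are prescriptions, and one patient can contribute several, so 1,745 is generous for a patient-level outcome.

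**2. Assumptions, not in the document.** Values at 3, 6, 9 and 12 months; SD 1; exchangeable correlation ρ of 0.5 or 0.7; design effect (DE) 1.29 carried over. The between-arm effect is δ(t), with d = 0.10 SD.

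**3. Post-index values only, effect constant at d.**

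- Linear time: the slope numerator is Σ(t − 7.5)·d = d × (−4.5 − 1.5 + 1.5 + 4.5) = 0.
- Time as a factor: Σ(δ − mean δ)² = 0, so the noncentrality is 0.
- Power = 5% in both cases. No choice of d, ρ, n or DE changes this.
- Adding baseline as a covariate does not change it either while the interaction remains the effect parameter.

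**4. Post-index values only, effect growing linearly to 0.10 SD at 12 months.**

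- Slope 0.10/12 = 0.00833 per month; variance 2(1 − ρ)·DE / (n × 45), where 45 = Σ(t − 7.5)².
- ρ = 0.5: SE 0.00405, z = 2.06, power 54%. ρ = 0.7: SE 0.00314, z = 2.65, power 76%.

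**5. Baseline included as time 0, constant effect from month 3.**

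- Linear time: slope 6d/90 = 0.00667; variance 2(1 − ρ)·DE / (n × 90). Here z = 2.33 or 3.00, power 64% or 85%.
- Time as a factor: noncentrality n × 0.8d² / [2(1 − ρ)·DE] on 4 df, i.e. 10.8 or 18.0, power 75% or 94%.

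**6. Baseline-adjusted difference at 12 months** (the type of model in Cost-effectiveness analysis).

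- Variance 2(1 − ρ²)·DE / n. SE 0.0333 or 0.0275, z = 3.00 or 3.64, power 85% or 95%.

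| Analysis | True effect | Power, DE 1.29 | Power, DE 1.0 |
|---|---|---|---|
| Interaction, post-index only | constant | 5% | 5% |
| Interaction, post-index only | growing (linear time) | 54–76% | 65–85% |
| Interaction, baseline as time 0 | constant (linear time) | 64–85% | 75–93% |
| Interaction, baseline as time 0 | constant (time as factor) | 75–94% | 87–98% |
| Baseline-adjusted, 12 months | constant | 85–95% | 93–99% |

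**7. Are the three CVR statements the same quantity?** Secondary outcome measures gives a level at one year. Effectiveness gives a difference in trajectory over several times. Cost-effectiveness analysis gives a level difference adjusted for baseline. For a constant effect d on post-index values, the second is 0 and the third is d.

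**The case against.** **Baseline is not expressly excluded.** A reader might infer that the pre-index values are definitely left out of the effectiveness model. The document does not say that. The outcome is called a reduction, which implies a starting value; baseline CVR is used elsewhere; and group x time is the usual effect parameter when baseline is time 0. On that reading step 5 applies and the loss of power largely goes. This stands, and it makes the point conditional. The wording still leans the other way: the responses are placed in follow-up, follow-up is defined as post-index, and the earlier data are given an adjustment role. The general covariate rule does not secure the baseline value, and the word also in the economic model suggests that baseline CVR is an addition to that rule.

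**The power figures can be over-read.** A reader might infer that the trial gives up 80 to 90 points of power. That needs baseline excluded, a constant effect, and a large enough effect. With the planned 3-point gain in initiation, a mean shift of 0.10 SD through extra initiation alone would require 0.10/0.03 = 3.3 SD per additional initiator. If each additional initiator changed by 10 units (assumed) with an SD of √200 = 14.1 units, the mean shift is 0.3 units. The baseline-adjusted SE at ρ = 0.5 is 0.0333 × 14.1 = 0.47, and power is about 10%, against 5% for the interaction. Larger effects would have to come through other routes, such as secondary adherence. This stands too.

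**Detail for the analysis plan.** Coding of time and visit windows can be left to an analysis plan that is not shown. Here, though, the article is not silent: it names the effect parameter, and it gives a different model for the same outcome elsewhere.

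**Two models may serve two purposes.** True in principle, and with baseline as time 0 the 12-month interaction contrast and the baseline-adjusted difference target the same quantity under randomisation. Neither the time 0 coding nor the 12-month contrast is stated.

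**Conclusion.** The point holds in conditional form. On the most direct reading, the effectiveness analysis of CVR and clinical parameters tests divergence within the follow-up year. For an effect present by the first follow-up value and then sustained, the expected interaction is zero and the test rejects at 5%; within that reading this is algebra. It does not follow that the analysis can see no effect at all: one that grows through the year remains detectable. All power figures other than the 5% depend on assumed visit times, correlations, effect size, sample size and design effect.

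Separately, the one-year outcome definition, the repeated-measures interaction and the baseline-adjusted economic model are not stated as one quantity, so the effectiveness result and the ICER can differ on CVR. Stating baseline as time 0 would cure most of the power loss, but the 12-month contrast would still have to be named to align the three sections.

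The weight is moderate. CVR is a secondary outcome, the clinical parameters rank below it, and initiation and its sample size are untouched. The change should be made before the data are analysed.

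**What to change.** In Effectiveness, name the between-arm difference at 12 months as the effect for CVR and for each clinical parameter, and state how the pre-index value enters. Either of two forms will do:

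- the pre-index value as a covariate, follow-up values as responses, time as a factor, and the group difference at 12 months as the estimate; or
- the pre-index value explicitly as time 0, time as a factor, and the 12-month group x time contrast as the estimate.

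The covariate form is the more precise for a single 12-month contrast: its variance is proportional to 1 − ρ², against 2(1 − ρ) for a change from baseline, i.e. 0.75 v 1.00 at ρ = 0.5 and 0.51 v 0.60 at ρ = 0.7.

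State in Cost-effectiveness analysis that the CVR effect in the ICER is this same estimand, and keep the one-year definition in Secondary outcome measures.

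The cost is wording and slightly more analysis work on data already to be extracted. Some pre-index values will be missing; the multiple imputation already planned can cover them.
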